### Study population

Participants are eligible for this study if they meet the following criteria:Parkinson’s disease duration ≤5 years, defined as time since the diagnosis made by a neurologist;18 years of age or older;Able to read and understand Dutch;Willing, competent, and able to comply with all aspects of the protocol, including follow-up schedules and biospecimen collections; andProviding written informed consent.

Patients with co-morbidity are explicitly NOT excluded from participation. Candidates will only be excluded in the case of existing co-morbidities that are sufficiently severe so as to hamper the interpretation of parkinsonian disability. Other exclusion criteria include contraindications to magnetic resonance imaging (MRI), pregnancy or breastfeeding, and/or nickel allergy (as components of the Study Watch contain this metal). For the lumbar puncture additional contraindications are defined, i.e., being treated with an anticoagulant medication or clinical evidence of structural cerebral abnormalities.

To guarantee a balanced study cohort, a stratification inclusion model will be applied, by gender (men/women), age (21–45;46–55; 56–65; ≥66 years) and disease duration (< 2½ years; ≥2½ years). Consequently, half of the cohort will have a disease duration of maximally 2½ years at the moment of inclusion, which will also allow us to the impact of very early signals and markers on disease progression.

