During the three in-clinic visits, detailed clinimetrics with multiple standardized evaluations for motor, neuropsychological, and other PD-related assessments are performed, while wearing the Verily Study Watch (see Table 1 for an overview). Some of the motor assessments are performed first in a clinically defined OFF state and repeated after the participant has taken the regular first morning dose of medication(s) and has subjectively reached a typical ON state. The medical examination and clinical assessments are videotaped with a static camera and/or recorded for audio signals, unless the subject declines. The video-recording are for local use only and will not be shared within the study. In addition, relevant biospecimens are collected, i.e., whole blood for plasma/peripheral blood mononuclear cells (PBMC)/serum/DNA/RNA, cerebrospinal fluid (CSF), and stool for longitudinal genotypic and phenotypic assays. CSF will be collected only at baseline and after 2 years and is the single optional element of the study protocol. Local anaesthesia will be provided to minimize patient burden and atraumatic needles will be used. Moreover, using advanced MRI, at baseline and after two years, indices of in vivo brain structure and function are obtained, using an extension of the UK Biobank protocol [20, 21]. The PPP MRI protocol captures structural MRI (T1 and T2-weighted imaging, diffusion tensor imaging (DTI) and quantitative susceptibility mapping (QSM)), resting functional MRI (fMRI), and two task-related fMRI studies. The tasks probe both primary brain dysfunction, i.e. basal ganglia dysfunction, as well as cerebral compensatory activity. An additional surface electromyography is performed during MRI scanning to monitor tremor, so artifacts can be removed [22]. Finally, to assess autonomic dysfunction, study subjects wear a Holter monitor during each in-clinic visit (except while being in the MRI scanner), and a 12-lead ECG is performed while the subject is supine. Blood pressure is measured in both supine and standing positions, from which the presence of orthostatic hypotension will be assessed.

**Table 1 Tab1:** Overview of included study measures and scales in the Personalized Parkinson Project

Method	Outcome	Scales	Visit 1 (Baseline)	Visit 2 (1 Year)^b^	Visit 3 (2 Years)^b^	After each visit^c^
Assessed by trial assessor	Motor functioning in OFF^a^ state	- MDS-UPDRS-III (including H&Y stage)	X	X	X	
		- Timed up-and-go test	X	X	X	

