#### Sample size considerations

For the first objective, we will test the association between potential biomarkers and the deterioration of PD on each of the two outcome domains. In this test, both the dependent and independent variables are continuous measures. In order to adjust for multiple testing issues (up to 55 biomarkers and two outcome measures) we will use a two-sided significance level of 0.05/(2 × 55), i.e., 0.00045 instead of 0.05. In order to detect an association with a correlation coefficient of at least 0.2 with a power of 90%, 565 patients are needed. Taking into account an attrition rate of 10% and missing data for approximately 3% of patients, we aim to include 650 patients in total. If additional novel biomarkers are selected for model consideration prior to the initiation of analysis, power of 80% will be retained with 100 or fewer biomarkers considered.

For the second objective we will use the dichotomous outcomes to estimate the required sample size. We will use a split sample approach to develop the model in the first half of the dataset and test it on the second half of the data. Therefore, if there are a total of 565 patients evaluable, as dictated by the power calculation for the first objective, there will be 282 patients available to assess the accuracy of the model in the test set. It is desirable to demonstrate that the accuracy is greater than 70%, i.e., the probability that the model correctly predicts whether the patient did or did not have an event using a pre-specified threshold, is larger than 70%. We will have 80% power to demonstrate that the model is more accurate than 70% if the true accuracy is 77% or higher. If sensitivity or specificity at a single cut point is lower than desired for clinical utility, power may be improved by assessing the AUC (area under the ROC curve) rather than the accuracy at a single threshold.

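### The 90% power stated for up to 55 biomarkers carries over to a CSF biomarker only if about 96% of retained patients give CSF, which is optional

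*Protocol article*

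**What the plan says.** All references are to the protocol article.

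- **Sample size considerations.** Objective 1 tests each biomarker against each of two outcomes. For "up to 55 biomarkers and two outcome measures" the article says "we will use a two-sided significance level of 0.05/(2 × 55), i.e., 0.00045 instead of 0.05". At that level, to detect "a correlation coefficient of at least 0.2 with a power of 90%, 565 patients are needed". The enrolment target follows: "Taking into account an attrition rate of 10% and missing data for approximately 3% of patients", "we aim to include 650 patients in total". This is the only power figure at r = 0.2 for the 55 biomarkers, and no type of biomarker is set apart.
- **Study procedures and assessments.** "CSF will be collected only at baseline and after 2 years and is the single optional element of the study protocol". Table 1 lists CSF among the biospecimens at visits 1 and 3.
- **Study population.** "For the lumbar puncture additional contraindications are defined, i.e., being treated with an anticoagulant medication or clinical evidence of structural cerebral abnormalities". The same section keeps patients with co-morbidity eligible unless it is severe enough to obscure parkinsonian disability. Patients who cannot have the puncture can therefore still be enrolled.

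No section gives an expected CSF uptake.

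**The concern.** The 3% allowance is plausible for an assessment that every participant must undergo. It is not reconciled with a sample that any participant may decline and that some enrolled participants may not give. For such a sample, uptake and contraindications set the share with data, and the article does not carry either into the power statement.

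What is at stake is how CSF results are read. If a CSF biomarker shows no association, the stated 90% power invites the conclusion that a correlation of 0.2 is unlikely, although the test may have had clearly less power than that. The data are also to be shared with outside researchers, who may rely on the published figure when planning CSF work.

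**Working it through.** **Inputs.** From Sample size considerations: two-sided alpha = 0.05/(2 × 55) = 0.05/110 = 0.000455; r = 0.2; power 90%; 565 evaluable; 10% attrition; about 3% missing; 650 enrolled. Assumed here, because the document does not give it: the share of retained patients who provide CSF.

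**Method.** Fisher z test of a correlation, with z for alpha/2 = 3.506, z for 90% power = 1.282, atanh(0.2) = 0.2027:

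- n = ((3.506 + 1.282)/0.2027)² + 3
- power = Φ(√(n − 3) × 0.2027 − 3.506)
- smallest r with 90% power = tanh((3.506 + 1.282)/√(n − 3))

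**Step 1: reproduce the plan.** The first formula gives n = 561, against the stated 565. Power at 565 is Φ(23.707 × 0.2027 − 3.506) = 90.3%. A noncentral t calculation gives 90.6%, and adjusting for two covariates does not change that. For enrolment, 565/0.87 = 649.4, which rounds up to 650. The plan's figures are right.

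**Step 2: find the slack.** After 10% attrition, 650 × 0.90 = 585 patients remain. Since 561 of them must have the biomarker, 24 may lack it: 24/585 = 4.1%. Below about 96% uptake, power is under 90%. It is under 80% when n is below 463, that is, when about 21% of the 585 lack CSF (1 − 463/585 = 0.209).

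**Step 3: show a range.** Non-uptake of CSF takes the place of the 3% missing-data allowance, so the base is 585. Applying uptake to 565 instead would count the 3% as well as the non-uptake.

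| Assumed CSF uptake | n = 585 × uptake | Power at r = 0.2 | Smallest r with 90% power |
|---|---|---|---|
| 95% | 556 | 90% | 0.20 |
| 90% | 526 | 87% | 0.21 |
| 80% | 468 | 81% | 0.22 |
| 70% | 410 | 72% | 0.23 |
| 50% | 292 | 48% | 0.27 |

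Example at 80%: √(468 − 3) = 21.564; 21.564 × 0.2027 − 3.506 = 0.865; Φ(0.865) = 81%; tanh(4.788/21.564) = 0.218.

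At 95% uptake the unrounded power is 89.6%, so the shortfall there is trivial. If uptake is applied to 565 instead, power at 80%, 70% and 50% is 79%, 70% and 45%, two to three percentage points lower.

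**The case against.** **The article does not list the 55 biomarkers.** This is true. That CSF markers are among them is an inference, and none of the example hypotheses under Statistical analyses names one. The inference is strong, because CSF is collected as a biospecimen for longitudinal assays and the Discussion adopts a broad biomarker definition. It is still not stated, so the point is conditional: it applies to any CSF biomarker in the set.

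**The 3% is given per patient, not per biomarker.** This is also true. It could describe missing outcome scores. If so, there is no stated allowance for missing biomarkers at all, and the power statement still presumes near-complete biomarker data.

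**Uptake is unknown.** This stands, and it limits what can be said about size. A reader might infer that CSF tests are badly underpowered. The document does not support that: at 95% uptake almost nothing is lost, and at 80% the detectable correlation moves only from 0.20 to 0.22. Equally, nothing in the document supports uptake of 96% or more.

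**These are details for the full protocol or SAP.** That is fair for the biomarker list and for the expected uptake, and their absence is not criticised here. The criticism is that the article publishes a power figure without exception while its own sections on study population and procedures describe a sample to which the figure need not apply.

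**A confidence interval for a CSF result would show the actual precision.** It would, and this softens the risk of misreading. It does not correct the stated power.

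**Objective 2.** A reader might infer that the prediction model would shrink to the patients with CSF, and that the 282-patient test half would shrink with it. The document does not support this. It does not prescribe complete-case analysis, it selects no CSF predictor, and it allows the variable list to be trimmed before analysis. Leaving CSF out of the primary model would be a modelling preference, not the correction of an error.

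**Conclusion.** The point holds as a fault in the scope of a stated power, and it should be fixed. It is not an arithmetic error: 565 and 650 both reproduce. Power for biomarkers from the mandatory assessments, the significance level, the recruitment target and the objective 1 model are all unaffected.

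The threshold of about 96% follows from the plan's own figures and needs no assumed uptake. The size of the loss below that threshold does need one, and over 95% to 50% uptake it runs from negligible to a power of about one half. The conclusion rests on two assumptions: that at least one CSF biomarker is among the 55, and that each CSF association is tested in the patients who gave a sample.

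**What to change.** In Sample size considerations:

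1. Say that 90% power at r = 0.2 applies to biomarkers from the mandatory assessments.
2. For CSF biomarkers, state a separate power at r = 0.2, or the smallest correlation detectable with 90% power, at the expected uptake. If collection is far enough advanced, use the observed uptake.

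The cost is two sentences and one short calculation. No extra patients are needed, and neither the significance level nor the analysis model changes. The downside is a less favourable stated power for CSF biomarkers.

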### Statistical analyses

The primary objective of this study is to evaluate the rate of disease progression and, ultimately, to evaluate treatment response with respect to the presence of both established and potential biomarkers. More specifically, we will address two objectives in the short term:The individual associations between potential biomarkers and disease progression in Parkinson’s disease, with progression being expressed in terms of rate of decline in two key outcome domains of the disease, i.e., motor functioning and cognitive functioning.The prediction of disease progression after 1 year and 2 years on each of the two outcome domains.

Motor functioning will be determined using the score from the motor section (part III) of the Movement Disorders Society-sponsored revision of the Unified Parkinson’s Disease Rating Scale (MDS-UPDRS) [37], measured in the OFF state. Cognitive functioning will be determined using the score from the Montreal Cognitive Assessment scale (MoCA), a scale for global cognitive abilities that is validated for use in Parkinson’s disease [38].

For each of the two outcomes, the prediction will be made for absolute change scores (as a continuous measure) and clinically important change scores or clinically important threshold (as a dichotomous measure). For motor functioning, the dichotomous measure is a change of at least 5.5 [39, 40]. For cognitive functioning, the dichotomous measure is a follow-up score below 23.5 [41]. Both will be calculated over the first year of follow-up, as a measure for short-term disease progression (hence with direct clinical relevance for near-term treatment decisions), and over 2 years of follow-up, as a measure for mid-term prognosis.

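### Objective 2's only numerical bar, pooled accuracy above 70%, ignores the event rate, so a rule predicting no event for everyone can meet it when events are few

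*Protocol article*

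**What the plan says.** Under Sample size considerations, the article plans to build the model in one half of the data and test it in the other: "there will be 282 patients available to assess the accuracy of the model in the test set". The aim is put as "It is desirable to demonstrate that the accuracy is greater than 70"%. Accuracy is defined as "the probability that the model correctly predicts whether the patient did or did not have an event using a pre-specified threshold, is larger than 70"%, so correct predictions of events and of non-events are pooled. The power statement reads: "We will have 80% power to demonstrate that the model is more accurate than 70% if the true accuracy is 77% or higher".

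Statistical analyses defines the two events. "For motor functioning, the dichotomous measure is a change of at least 5.5" points, and for cognition "the dichotomous measure is a follow-up score below 23.5". Each is assessed over 1 year and over 2 years, which makes four endpoints. No event rate is given for any of them, and no endpoint has its own bar.

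The article adds that, if sensitivity or specificity at one cut point is too low to be clinically useful, "power may be improved by assessing the AUC (area under the ROC curve) rather than the accuracy at a single threshold". It gives no target value for sensitivity, specificity or the AUC.

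**The concern.** Pooled accuracy at one cut-off mixes two things: how well the model separates patients, and how common the larger class is. A rule that uses no data and assigns everyone to the larger class has accuracy equal to the larger of the event rate and its complement. A fixed 70% therefore sits below the no-information level for some event rates and far above it for others.

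Two consequences follow. If an endpoint is rare, or very common, a result above 70% may carry no evidence that the model predicts anything. And the same 70% means something different for each of the four endpoints: it is demanding near 50% events and empty at 10%. The power statement inherits the problem, because 77% can be an informative alternative or simply the share of patients without the event.

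**Working it through.** **Inputs.** From Sample size considerations: test set n = 282, null accuracy 0.70, alternative 0.77, stated power 80%. Not in the article: alpha and sidedness for objective 2 (the level of 0.00045 belongs to objective 1) and the event rate e. I assume two-sided 5%, that is one-sided 2.5%, with one-sided 5% as a variant, and take e from 10% to 50%.

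**1. Reproducing the stated power.** One-sample proportion test, normal approximation with the variance at the alternative:

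- SE = √(0.77 × 0.23 / 282) = 0.0251
- power = Φ(0.07 / 0.0251 − 1.96) = Φ(0.83) = 79.8%

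This matches the stated 80%, so the criterion has been read as intended. The exact binomial test at one-sided 2.5% needs at least 213 of 282 correct (size 0.0233) and has 74.7% power at 77%. At one-sided 5% it needs 211 (size 0.0427) and has 82.7% power.

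**2. True accuracy of a constant rule.** Predicting no event for everyone gives accuracy 1 − e.

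- 1 − e > 0.70 whenever e < 0.30
- 1 − e = 0.77 when e = 0.23, which is the alternative the study is powered for

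Predicting an event for everyone gives accuracy e, so the mirror image holds above 70% and at 77%.

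**3. Chance that the no-event rule passes the 70% test.** With 213 correct needed, the rule passes if the test set holds at most 282 − 213 = 69 events (69/282 = 24.5%). The probability is P(X ≥ critical value) for X binomial with n = 282 and success probability 1 − e.

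| Event rate | True accuracy | One-sided 2.5% (≥ 213) | One-sided 5% (≥ 211) |
|---|---|---|---|
| 10% or 15% | 90% or 85% | about 100% | about 100% |
| 20% | 80% | 97.2% | 98.6% |
| 22% | 78% | 85.8% | 91.1% |
| 23% | 77% | 74.7% | 82.7% |
| 25% | 75% | 45.0% | 55.9% |
| 28% | 72% | 10.4% | 16.1% |
| 30% | 70% | 2.3% | 4.3% |
| 40% or more (to 50%) | 60% or less | about 0% | about 0% |

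**4. What a bar tied to the event rate would ask.** If the null were the majority-class rate max(e, 1 − e), the formula of step 1 gives the true accuracy needed for 80% power with 282 patients: 94.0% at 10% events, 90.0% at 15%, 85.8% at 20%, 83.2% at 23%, 77.0% at 30%, 67.8% at 40% and 58.2% at 50%. The article's 77% is the right alternative only when the event rate is 30%, or 70% by symmetry.

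**5. The same patients judged by AUC.** A constant rule has AUC 0.5 and balanced accuracy (0 + 1)/2 = 0.5 at every event rate. Against a null of 0.5 (Hanley–McNeil variance, two-sided 5%), the AUC detectable with 80% power is about 0.66 at 10% events, 0.62 at 20% and 0.60 at 50%.

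**The case against.** The best defence is that the article does not call 70% a pass mark. It says that exceeding it is desirable, and says so in a section on sample size. The formal assessment of objective 2 is described under Statistical analyses without naming a metric, and an analysis plan that is not shown may add more. That stands as to wording. But 70% is the only bar the article gives for objective 2, and the only one its power claim rests on.

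Second, the authors do consider sensitivity and specificity, and the no-event rule has sensitivity 0. So the quantity that exposes the rule is in view. The clause does not repair the criterion, because it is optional, serves to improve power and sets no minimum.

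Third, no event rate is stated. A reader might infer from the limit of 5 years since diagnosis and the exclusion of diagnosed dementia that events will be rare. The article does not establish this. The cognitive event is a status at follow-up, so patients already below the cut-off at baseline can count. No minimum MoCA at entry is stated, there is an age stratum of 66 and over, and co-morbidity is admitted. Nothing in it points to a low rate for the motor event. It does allow that events in the training half may be too few for a strong model, which shows that a low count was contemplated but not that it is expected.

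Finally, a reader might want objective 2 to show that biomarkers add to clinical variables. The article defines objective 2 as prediction of progression and places biomarker association in objective 1, so a lack of incremental value is not a failure of this criterion.

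**Conclusion.** The point holds in conditional form. The stated criterion is not tied to the event rate and can be met by a rule with no predictive content. Under an exact one-sided 2.5% test, such a rule is nearly certain to pass at 20% events or fewer, passes about three times in four at 23%, and seldom passes at 28% or more. One-sided 5% raises the 23% figure to 83%.

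A reader might infer that the no-event rule always clears the bar below 23% events, or that the study will in fact declare an empty success. The documents support neither. The value of 23% is where the rule's true accuracy equals the planned alternative, not a sharp limit, and the actual event rates are unknown. Between about 30% and 70% events the 70% bar does exclude constant rules.

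The conclusion rests on an assumed alpha and an assumed range of event rates. The thresholds of 30% and 23% are plain arithmetic and need neither.

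**What to change.** Make test-set AUC, or balanced accuracy, the primary criterion for objective 2. Require its lower confidence limit to exceed a pre-stated value above 0.5, state the alpha, and give the power for that criterion over a range of event rates. The detectable AUCs in step 5 are for a null of 0.5, so a higher bar will need a higher true AUC.

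If raw accuracy is kept, report it with sensitivity and specificity, and compare it with the majority-class rate of each endpoint rather than with 70% alone. As a formal test this is severe when events are few (94.0% true accuracy needed at 10% events) and could fail a useful model, which is a reason to prefer the AUC.

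A comparison with a clinical-only model, if wanted, belongs as a secondary analysis. It should be a paired AUC comparison that allows for the sampling error of both AUCs.

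The cost is a changed criterion and a recomputed power statement, with no new data to collect. Success may be harder to show when events are few.

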## Discussion

The key purpose of the Personalized Parkinson Project is to contribute to the understanding of the differences in etiology, pathophysiology, phenotypic diversity, and disease progression among individual PD patients. Although previous cohort studies have largely contributed to elucidate the differences between PD patients and healthy control subjects [8, 45–47], we remain unable to understand the basis for the large diversity of phenotypes and variability in progression rates among PD patients. It remains unclear why some PD patients stay functional and independent long into the disease, while others progress to significant motor and/or cognitive impairment and are unable to live unassisted relatively early in the course of the disease. The 2-year follow-up captures inter-individual differences in the speed of disease progression on numerous clinically relevant outcomes, including motor- and non-motor symptoms and endpoints that are relevant in the earlier phases of the disease, such as the ability to work.

The PPP has several unique elements: an unbiased approach to patient selection, with purposely broad inclusion criteria (also allowing for presence of co-morbid conditions); repeated clinical, molecular, and imaging data collection performed at a single center; and multi-dimensional analysis to uncover novel biomarkers of PD. A broad biomarker definition will be applied, in line with the recently proposed modular set of biomarker assessments [48]. In addition, participants will be followed for 2 years using a wearable multi-sensor device, which creates the opportunity to continuously monitor aggregated features (e.g., daily and weekly activity level, mean daily pulse rate and its variability, average sleep efficiency per day) to characterize each participant over time. The very liberal inclusion criteria, where participants with co-morbidities are encouraged to join, allow us to collect data from “real-life” patients and explore how co-morbidities impair the overall expression of PD. Moreover, although we aim for a unique dataset, to the extent possible we have harmonized data collection with previously performed cohort studies including the Parkinson Progression Marker Initiative [5], Luxembourg Parkinson’s Study [11] and the Oxford Parkinson Discovery Cohort [12]. In this manner we also support initiatives such as the Critical Path for Parkinson’s Consortium (CPP), that aim to create integrated unified databases, thus allowing to increase sample sizes or add control populations and further enhance research.

Furthermore, the PPP cohort will contribute data managed through an unprecedented digital security system, which will allow sharing of data with researchers worldwide with maintenance of participants’ privacy. The digital security system is based on a multi-point, privacy-by-design strategy: (a) participants provide informed consent, also for the important element of data sharing; (b) signed contractual agreements with researchers are in place to ensure that no attempts towards de-identification or commercialization of the raw data will be attempted; (c) governance policies restrain access to the data to only qualified researchers; (d) an innovative pseudonymization and encryption process is applied [35]; and (e) a protected research environment is used to analyze the data.

Lastly, powered by Verily’s analytics capabilities, the PPP will allow us to address research questions of great scientific and clinical value to improve our understanding of PD pathology and variation between patients in terms of disease progression, therapy response (both efficacy and tolerance), and survival. Though we will not be able to adjust for normal age-related changes due to the lack of a matched control group, the PPP data will help to identify new biomarkers to predict differences in prognosis and treatment response between patients, an important step to improving existing treatments, developing new therapeutic approaches, and providing PD patients with a more precise and personalized disease management approach. Finally, this cohort will serve as a source of data for qualified researchers worldwide, allowing them to use their research capacity to further address and enhance the main aims of this study.

